## Abstract

**Background:**

A worksite prevention program was developed to promote the work ability of construction workers and thereby prolong a healthy working life. The objective of this paper is to present the design of a randomized controlled trial evaluating the effectiveness of that intervention program compared with usual care for construction workers.

**Methods:**

The study is designed as a randomized controlled trial with a follow-up of one year. Employees eligible for this study are construction workers performing actual construction work. The worksite intervention will be compared with usual care. This intervention was developed by using the Intervention Mapping approach and consists of the following components: (1) two individual training sessions of a physical therapist to lower the physical workload, (2) a Rest-Break tool to improve the balance between work and recovery, and (3) two empowerment training sessions to increase the influence of the construction workers at the worksite. Outcome measures are assessed at baseline, 3, 6, and 12 months. The primary outcome measures of this study are work ability and health-related quality of life. Secondary outcome measures include need for recovery, musculoskeletal complaints, work engagement and self efficacy. Cost-effectiveness will be evaluated from the company perspective. Moreover, a process evaluation will be conducted.

**Discussion:**

The feasibility of the intervention and the study has been enhanced by creating an intervention program that explicitly appeals to construction workers and will not interfere too much with the ongoing construction. The feasibility and effectiveness of this worksite prevention program will be investigated by means of an effect- and a process evaluation. If proven effective, this worksite prevention program can be implemented on a larger scale within the construction industry.

**Trial Registration:**

NTR1278

## Background

In order to face the challenges of the aging working population and to extend the healthy working lives of the workers, the construction industry in the Netherlands has reason to pay attention to maintaining and promoting work ability [1,2]. Work ability is defined as how well workers can perform their jobs at present and in the near future, and is the result of the interaction between the individuals' capacity and the work demands [3,4]. Work ability is determined by personal factors like health, functional capacity and job satisfaction and occupational factors like physical work demands and the work organization [4-6].

Because of the high physical workload and the health risks involved [7-10], construction workers run relatively high risks to suffer an impaired work ability [2,4]. To change things for the better, health promoting activities to maintain and improve the work ability seem necessary. Until now, most health promotion programs in the construction industry have focused on either improving the health of construction workers by means of a lifestyle program [11,12] or on decreasing the work demands by means of ergonomic measures [13,14]. Only one intervention study in the construction industry was found that explicitly aimed to improve the work ability. That single-component intervention consisting of a counseling and education program for construction workers at risk for disability pension showed a slight but not significant improvement of the work ability [15].

Based on the fact that work ability is a multidimensional concept, it was hypothesized that a multidimensional intervention approach could potentially be more effective. To our knowledge, such interventions have not yet been undertaken in the construction industry. Therefore, in our study a multidimensional intervention was developed, taking into account the individual factors as well as the work environment, in order to promote the work ability ([name] et al., Using intervention mapping to develop a worksite prevention program for construction workers, submitted). The intervention was developed by means of the Intervention Mapping approach which is based on theoretical information from literature and practical information from stakeholders [16]. This resulted in an intervention tailored to the needs of the construction workers. This paper presents the design of the worksite prevention program illustrating the recruitment of the workers, the feasibility of the study, and the attractiveness of the program for the workers.

## Methods

### Study design

A Randomized Controlled Trial is performed in order to evaluate the effectiveness of the intervention. This trial is carried out to evaluate whether the worksite prevention program for construction workers improves construction workers' work ability and their health-related quality of life. Construction workers at the worksites allocated to the intervention group receive the worksite prevention program during six months; those allocated to the control group receive no intervention (i.e. usual care). Participants are followed for one year. Primary and secondary outcomes are measured at baseline, and 3, 6 and 12 months after baseline measurement. The study protocol was approved by The Medical Ethics Committee of the VU University Medical Center (Amsterdam, The Netherlands).

### Study population

The study population consists of construction workers performing actual construction work (i.e., blue collar workers). These workers are contracted by six companies which are specialized in house-, commercial- or industrial building. The other inclusion criteria were (1) available for the study for the following 12 months, (2) sufficient mastery of the Dutch language and (3) having signed a written informed consent. No exclusion took place based on age or gender.

### Recruitment of the study population

In order to successfully accomplish an intervention program at the worksite, strong support and participation of different company levels (managers, supervisors and workers) was considered essential. At the start of the project, we therefore recruited the top-management of the six companies who committed themselves to the project by signing a letter of intent. Additionally, they agreed that their workers (supervisors and construction workers) were allowed to participate in the program during working hours. The managers informed all supervisors about the aim of the intervention and the intervention components. Finally, the researchers informed all workers at the worksite about the intervention program by an oral presentation and by handing out a letter with the content of the program.

### Randomization

Cluster randomization took place at the level of department within each company. In order to avoid intervention group contamination, to accommodate a potential work-related intervention, to obtain maximal cooperation of employers and employees, and to enhance participants' compliance, cluster randomization was considered the best randomization strategy for this study. The randomization was performed by a research assistant who had no prior information about the departments. For practical reasons, randomization was performed before the baseline measurements. Because the intervention takes place at the worksite, the participants, their supervisors and the trainers cannot be blinded to the group assignment.

### Intervention

The intervention was developed using the Intervention Mapping approach [16]. Intervention Mapping ensures participation and consultation of all stakeholders (employers, supervisors, workers, health professionals, and providers). The development of the detailed program plan was based on three key points: (1) feasibility: a program which could be executed at the worksite, not interfering too much with the ongoing construction work (2) attractiveness for workers: the program should be geared to the workers' perception of their work environment (3) a standardized protocol for a sound scientific evaluation. Based on the first step of Intervention Mapping, two program objectives were defined: (1) the program should improve the balance between the physical workload and the need for recovery and (2) the program should increase the range of influence of construction workers at the worksite. Following the steps of Intervention Mapping, the program objectives were transformed into an intervention program of six months. An extensive description of the Intervention Mapping process and the content of the intervention has been described elsewhere ([name] et al., Using intervention mapping to develop a worksite prevention program for construction workers, submitted). The intervention consists of a physical component and a mental component. At the start of the program, the intervention is introduced to the workers and their supervisors by a 3-minute lasting video showing the content of the intervention and the accompanying components. This video uses the metaphor of a soccer game to introduce the underlying principles of the intervention program.

The physical component consists of (1) two individual training sessions by a physical therapist and (2) a "Rest-Break Tool". To reduce the physical workload, the worker receives two training sessions by an occupational physical therapist. During the first training, the therapist assesses work style, working methods, and the balance between physical load and rest breaks, and makes an assessment of the associated health risks. This is done by means of a quick scan questionnaire and a 15-20 minute observation of the worker. Based on the assessment, the therapist gives individual advice on how to reduce the physical workload, focusing on the improvement of the work style, the work methods and/or the rest breaks. At the end of the first training session, the physical therapist writes down a maximum of three recommendations for the worker on a pocket-size card. Before the training session begins, the therapist meets the supervisor of the worksite to inform him about the purpose of his visit. After training all participating workers at one site, the physical therapist meets the supervisor in order to discuss the group results. During the second visit, after four months, the therapist discusses the experiences so far and evaluates the impact of the advice of the first training with the worker. If necessary, the physical therapist and the worker adjust the advice. Second, a Rest-Break Tool was developed that focuses on fatigue and need for recovery. The aim of the Rest-Break Tool is to raise awareness about the importance of reducing fatigue among workers by taking flexible rest breaks and to stimulate to actually take rest breaks in order to reduce fatigue. The Rest-Break tool was set up as a flowchart and consists of four steps: (1) the expectations of the workers about their own fatigue at the end of the working day, (2) short term advice to take mini rest breaks (20-60 seconds) or an additional break of ten minutes, (3) selection of possible causes of fatigue and (4) long term advice about structurally lowering fatigue. The Rest-Break Tool is introduced and explained to the workers by the therapist during the first visit. The workers are asked to fill in the tool weekly, alone or with colleagues, and to discuss the results with their supervisor. At the start of the program, the supervisors receive a folder with the Rest-Break Tools to hand out to the workers at a fixed time each week. A text message by the mobile phone is sent weekly as a reminder to all supervisors.

For the mental component of the intervention, workers receive two interactive empowerment training sessions. Due to practical reasons, the duration of the training is limited to one hour. The empowerment trainer is present at the worksite before the training to get an impression of the worksite. The training is aimed at improving the range of influence of the workers at the worksite. The workers are taught how to change their attitude from a passive towards a more proactive attitude by increasing the self-efficacy regarding (1) taking responsibility for their own health, (2) discussing with colleagues about the responsibility for their own behavior (e.g., taking rest breaks, asking for assistance during lifting tasks) and (3) improving the communication with the supervisor. A proactive attitude supposes that workers control and change possible adverse working conditions by themselves. The training consists of five components; (1) an introduction of the concept of self-efficacy within the construction industry, (2) an introduction of the training as part of the program, (3) an explanation about how to change, in general, a passive attitude towards a more proactive and positive attitude, (4) a list of topics (e.g., good teamwork, more communication with supervisor, more rest breaks) workers would like to change during the intervention, and (5) an action plan written down on a poster. The training is tailor-made which means that the five steps are just a rough outline of the training. The therapist meets the supervisor before the training sessions, to inform him about the purpose of his visit and to invite him to (partly) attend the meeting. After four months, during a follow-up meeting, the empowerment trainer and workers discuss, evaluate and reconsider the action plan and results that are already booked.

Figure 1 presents the timeline of the current study including the different intervention components and the measurements. For feasibility reasons, all training sessions are organized within the existing so-called "toolbox education system" in the construction industry. The toolbox education system consists of at least 10 obligatory health and safety training sessions for workers, which have to be organized by employers in the construction industry each year. These training sessions are necessary in the construction industry to obtain an official safety and health certificate.

**Figure 1 F1:**
[figure not shown]
**Flow chart of the intervention program**.

### Co-interventions

It is pointed out to the companies that participation in other intervention studies or programs aimed at health promotion (e.g. lifestyle programs, adjustments of the equipment, organizational changes) is not allowed during this study. At 12 months follow-up, managers are asked if any other intervention took place during the period of the current study. Some other health care use, like visiting a physical therapist, is regarded as usual care.

### Compliance and loss to follow up

All participants in this study receive a questionnaire at baseline and a follow-up at 3, 6 and 12 months after baseline measurement. Participants that withdraw from the intervention program are followed and receive the questionnaire at the given time points. To register the reasons for withdrawal, all participants are asked if they voluntarily want to give their reason(s) for discontinuing the intervention.

To minimize loss-to-follow up, the researchers distribute and collect the questionnaires at the worksite. In case of absence from work of the participants, the supervisors at the worksite are asked to hand out the questionnaire to the participants later on and to encourage the participants to complete the questionnaire and to send the questionnaire back in a stamped and addressed envelope. If the questionnaire is not received within three weeks, a new questionnaire is sent to the worker.

### Incentives

It is well-known that maintaining participants is a difficult process in intervention studies [17]. Therefore, incentives are distributed among the participants to make participation more attractive and to minimize loss to follow up. After the first empowerment training the participants receive a mug with the study logo. All participants receive playing cards with the study logo after the second questionnaire (at three months follow-up). Moreover, as a reminder of the project, posters are distributed after the first and second empowerment training.

### Sample Size

The sample size was calculated according to the number of cases needed to identify an effect on health-related quality of life. Because the outcome measure SF-12 has rarely been used in intervention studies among the general population, the SF-36 [18,19] was used for the sample size calculation. Calculated effect sizes range (Cohen's D [20]) from 0.58 (which can be considered 'medium' according to effect size conventions) to 0.96 (considered large) [18,21]. Because of the cluster randomization design, a certain loss of efficiency associated with cluster randomization relative to individual randomization was taken into account [22]. An effect size of 0.40 was considered to be the lower boundary of a 'medium' effect size [20]. This effect size can be detected with a power (1-β) of 0.80 and a two-tailed alpha of 0.05 with two groups of 100. Taking a loss to follow up of about 10% into account, we need to recruit a total of 220 participants.

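### The 80% power claimed for an effect of 0.40 with two groups of 100 is the individually randomised figure, although the text says clustering was allowed for

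*Protocol article*

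**What the plan says.** The unit of randomisation is the department: "Cluster randomization took place at the level of department within each company" (Randomization). The Statistical analyses section accordingly plans a multilevel model with time, worker and department as levels.

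The Sample Size section sizes the trial on health-related quality of life, in this order:

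- It reports effects from earlier SF-36 work: "Calculated effect sizes range (Cohen's D [20]) from 0.58", running up to 0.96.
- It says that, because of the cluster design, "a certain loss of efficiency associated with cluster randomization relative to individual randomization was taken into account".
- It names the target: "An effect size of 0.40 was considered to be the lower boundary of a 'medium' effect size".
- It states the result: "This effect size can be detected with a power (1-β) of 0.80 and a two-tailed alpha of 0.05 with two groups of 100".
- It adds about 10% for loss to follow-up, giving 220 recruited.

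The only numerical inflation shown is the one for loss to follow-up. No design effect appears in the calculation.

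**The concern.** The paragraph makes two statements that cannot both hold for the same effect size. One says clustering was allowed for. The other gives a group size that is almost exactly what a two-sample comparison of independent workers needs for 0.40.

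If the number contains no allowance, the trial has less than 80% power for 0.40 whenever workers in a department resemble each other. A null result would then be read as coming from a trial adequately powered to find 0.40 on a primary outcome, when the effect it can reliably detect is larger.

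**Working it through.** **Inputs from the Sample Size section.** Two-sided alpha 0.05 (z = 1.96), power 0.80 (z = 0.8416), standardised effect 0.40, 100 analysed per group, lowest literature effect 0.58.

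**Reproducing the stated figure without clustering.**

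n per group = 2 × (1.96 + 0.8416)² / 0.40² = 98.1. The t-test version gives 99.1. Power at 100 per group is 0.807 (normal) or 0.804 (t-test). The stated 100 is the unclustered requirement, rounded up. Neither one-sided alpha (78 per group) nor 90% power (132 per group) fits.

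**Room left for a design effect (DE).** 100 / 98.1 = 1.02. With DE = 1 + (m − 1) × ICC and, for illustration, m = 10 workers per department, that corresponds to an ICC of 0.02 / 9, or about 0.002.

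**Size of the shortfall (assumed inputs).** The documents give neither the number of departments k nor an ICC, so I take k = 12, 24 and 36 and ICC 0.01 to 0.05, with m = 200 / k. The comparison is unadjusted and at one time point.

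- Power (normal) = Φ(d × √(100 / (2 × DE)) − 1.96).
- Power (k−2 df) uses the non-central t distribution with the same non-centrality.
- Detectable effect (normal) = 2.8016 × √(2 × DE / 100).

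Example, k = 12 and ICC 0.05: m = 16.67 and DE = 1 + 15.67 × 0.05 = 1.78. The non-centrality is 0.40 × √(100 / 3.57) = 2.12, so power = Φ(0.16) = 0.56. With 10 df it is 0.48.

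| Departments | ICC | DE | Power for 0.40, normal / k−2 df | Detectable at 80%, normal / k−2 df | Power for 0.58, normal / k−2 df |
|---|---|---|---|---|---|
| 12 | 0.01 | 1.16 | 0.75 / 0.66 | 0.43 / 0.47 | 0.97 / 0.93 |
| 12 | 0.02 | 1.31 | 0.69 / 0.61 | 0.45 / 0.50 | 0.95 / 0.90 |
| 12 | 0.05 | 1.78 | 0.56 / 0.48 | 0.53 / 0.59 | 0.87 / 0.79 |
| 24 | 0.01 | 1.07 | 0.78 / 0.74 | 0.41 / 0.43 | 0.98 / 0.97 |
| 24 | 0.02 | 1.15 | 0.75 / 0.71 | 0.42 / 0.44 | 0.97 / 0.96 |
| 24 | 0.05 | 1.37 | 0.68 / 0.64 | 0.46 / 0.49 | 0.94 / 0.92 |
| 36 | 0.01 | 1.05 | 0.79 / 0.77 | 0.41 / 0.42 | 0.98 / 0.97 |
| 36 | 0.02 | 1.09 | 0.77 / 0.75 | 0.41 / 0.43 | 0.98 / 0.97 |
| 36 | 0.05 | 1.23 | 0.72 / 0.70 | 0.44 / 0.45 | 0.96 / 0.95 |

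**Testing the step from 0.58 to 0.40 as the allowance.** An effect of 0.58 needs 2 × 2.8016² / 0.58² = 46.7 per group (t-test 47.6). So 100 per group would absorb a DE of 100 / 47.6 = 2.1, the same as (0.58 / 0.40)², if the number of departments did not matter. Solving for 80% power at 0.58 with k−2 df gives a tolerable DE of about 1.74 with 12 departments and 1.96 with 24.

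**The case against.** The strongest defence is the order of the paragraph. The clustering sentence stands between the literature effects and the choice of 0.40, which suggests that the authors planned for 0.40 instead of 0.58 as their way of absorbing the loss. On that reading clustering was not forgotten, and the last column of the table shows good power for 0.58 almost throughout. This stands as an account of what may have been intended. It does not save the sentence. The text justifies 0.40 as the lower edge of a medium effect, not as a deflated 0.58, and it attaches the 80% to 0.40 itself.

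Baseline adjustment or the repeated measurements might recover some power. That is possible, but the sample size paragraph invokes neither.

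A reader might also infer more than the documents support:

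- **That the trial is demonstrably underpowered, or that clustering is ignored throughout.** Power for 0.58 is reasonable over the assumed range, and the planned analysis includes department as a level.
- **That one of the tabulated values is this trial's power.** Each depends on an assumed ICC and number of departments. With 36 departments and ICC 0.01 the loss is only about one point on the normal approximation. A journal article may leave those inputs to the full protocol, so their absence alone is not the fault.
- **That the attrition step is a further error.** The article says: "Taking a loss to follow up of about 10% into account, we need to recruit a total of 220 participants". Keeping 200 of 220 is a loss of 20 / 220 = 9.1%, which is about 10%. At exactly 10%, 99 per group still gives 80.0% (t-test) without clustering. Nothing turns on it.

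**Conclusion.** The point holds as a contradiction within the Sample Size section. The group size stated for 0.40 contains essentially no allowance for clustering (DE at most about 1.02), so the 80% claim for that effect does not describe a trial randomised by department.

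The direction is firm for any DE above 1.02; the amount is not. For 12 to 36 departments, ICC 0.01 to 0.05 and an unadjusted single-time-point comparison, power for 0.40 is about 0.56-0.79 (normal) or 0.48-0.77 (k−2 df). The effect detectable with 80% power is about 0.41-0.53 or 0.42-0.59 respectively. If 0.58 was the real target, power is about 0.87-0.98 (normal) or 0.79-0.97 (k−2 df) over the same range. The trial is then reasonably sized for that target, and only the claim for 0.40 is wrong.

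**What to change.** Keep enrolment at 220 and rewrite the paragraph in one of two ways.

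1. **If 0.40 is the target.** Say that two groups of 100 give 80% power for 0.40 only under individual randomisation. Then report power and detectable effect from DE = 1 + (m − 1) × ICC, using the actual number and size of the randomised departments, a stated ICC range and k−2 degrees of freedom. Any gain claimed from baseline adjustment or repeated measures should be shown explicitly.
2. **If lowering 0.58 to 0.40 was the clustering allowance.** Say that the trial is powered for 0.58 after clustering and delete the claim for 0.40. Give the tolerable design effect with k−2 degrees of freedom (about 1.74 with 12 departments, 1.96 with 24), not the 2.1 that ignores the number of departments.

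The cost is one rewritten paragraph and a less favourable stated power. No participants are added and the analysis does not change.
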